### Outcomes {12}

Table 3 presents an overview of the time points for each outcome measurement.

**Table 3 Tab3:** Measures

	*Measures*				Measurement			
	Measure	Items	Respondent*	Type	T(0)	T(1–11)	T(12/14)	T(13)
Child PTSD	CAPS-CA		c	Interview	*			*
	CRIES	13	cp	Questionnaire	*	*	*	*
	TSCC	54	c	Questionnaire	*		*	*
Child functioning	SDQ	25	cp	Questionnaire	*		*	*
	CDI	28	c	Questionnaire	*		*	*
	CDC	20	p	Questionnaire	*		*	*
Parent functioning	NOSI-K	25	p	Questionnaire	*	*	*	*
	Trauma-informed	6	p	Questionnaire	*		*	*
	IES-r	22	p	Questionnaire	*		*	*
	YAS-R	29	p	Questionnaire	*		*	*
	DPAS	9	p	Questionnaire	*		*	*
Structural emotional and physical safety	CTS	77	p	Questionnaire	*		*	*
	CTS-pc	27+39	c	Questionnaire	*		*	*
	PRTI	21	p	Questionnaire	*		*	*
	ACE-Q	10	p	Questionnaire	*		*	*
	New IPV incidents	8	cp	Questionnaire	*	*	*	*
	SIS	43	c	Questionnaire	*		*	*
	SIFS	7	c	Questionnaire	*		*	*
	SIM-PR	28	p	Questionnaire	*		*	*
	Security scales	15	cp	Questionnaire	*		*	*
	FIT	4 tasks	cp	Observation			*	
Total items child					232	21	232	232
Total items parent					335	46	335	335

Marked measures are part of routine outcome measuring

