The Security Scale [71, 72] is a 15-item self-report questionnaire for children between the ages of 8 and 18 and measures self-reported attachment security with their parents [73]. Children and parents (independently) report on responsiveness and availability of the parent in the parent-child relationship (attachment). Each item is rated on a 5-point Likert scale (1 = strongly agree, 5 = strongly disagree). An example item is *I feel my mother really understands me*. Several studies indicate adequate reliability and validity [74]. High internal consistencies for 10 and 12-year-olds (*α* = 0.82, *α* = 0.79) are reported [75]. Test-retest reliability over a 2-week period was high (*r* = 0.75) [73]. The Security Scale is related to other attachment measures [75]. In a Dutch sample, internal consistency for the child version was *α* = 0.81 [76].

The Family Interaction Task (FIT) [77] is an observational instrument that measures parent-child interaction and consists of four tasks in which parent and child are instructed to complete a series of interactive tasks together. The FIT consists of four structured tasks: (1) guessing words by getting clues, (2) etch a sketch, (3) conflict task, and (4) completing a difficult but solvable puzzle by untangling a fixed ring from a standard within 4 min. These tasks are designed to elicit variations in parental and adolescent autonomy-promoting behaviours and emotional affect. The tasks are originally developed for children in middle childhood, but the tasks have been adapted for adolescents. Rating scales range from 1 to 5 and a higher score indicates a greater presence of that particular construct. Ratings are based on the complete session. Each videotaped session is independently coded by two coders (researchers). Interrater reliability was adequate (*n* = 101, ICC range .87–.94) in a Dutch sample [76].

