## Statistical methods

### Statistical methods for primary and secondary outcomes {20a}

The measurement level of each variable is at least ordinal. We control for the duration and severity of family violence [96], child functioning, parental psychopathology [97], and new incidents of family violence as a priori potential confounders. Analyses will be performed using the latest version of the software package Statistical Package for the Social Sciences (SPSS). First, to determine whether changes on continuous measures are different per treatment, we use linear mixed models. Continuous measures with only one time point will be analysed with independent samples *T*-test. Changes in categorical outcomes over the course of treatment across the conditions are tested with generalized estimating equations (GEE). To handle missing data, we will use maximum likelihood estimation within the linear mixed model analyses. For the planned GEE, we will explore the possibilities to deal with missing data, depending on the amount, randomness, and type of data missing. Analyses will primarily be performed according to the principles of intention-to-treat; however, they will be repeated as per-protocol analyses (see Table 4).

**Table 4 Tab4:** Statistical analyses

*Statistical analyses*					
	Measure	Type of data	Timepoints	Statistical analysis	Subjects
Child PTSD	CAPS-CA	Categorical	3	GEE	ITT/PP
	CRIES	Continuous	4	Mixed models	ITT/PP
	TSCC	Continuous	3	Mixed models	ITT/PP
Child functioning	SDQ	Continuous	3	Mixed models	ITT/PP
	CDI	Continuous	3	Mixed models	ITT/PP
	CDC	Continuous	3	Mixed models	ITT/PP
Parent functioning	NOSI-K	Continuous	4	Mixed models	ITT/PP
	Trauma-informed	Continuous	3	Mixed models	ITT/PP
	TSI	Continuous	3	Mixed models	ITT/PP
	YAS-R	Continuous	3	Mixed models	ITT/PP
	DPAS	Continuous	3	Mixed models	ITT/PP
Structural emotional and physical safety	CTS	Continuous	3	Mixed models	ITT/PP
	CTS-pc	Continuous	3	Mixed models	ITT/PP
	PRTI	Continuous	3	Mixed models	ITT/PP
	ACE-Q	Continuous	3	Mixed models	ITT/PP
	New IPV incidents	Continuous	4	Mixed models	ITT/PP
	SIS	Continuous	3	Mixed models	ITT/PP
	SIFS	Continuous	3	Mixed models	ITT/PP
	SIM-PR	Continuous	3	Mixed models	ITT/PP
	Security scales	Continuous	3	Mixed models	ITT/PP
	FIT	Categorical	1	Independent samples T-test	ITT/PP

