Descriptive and exploratory analyses will be carried out by standard methods. All continuous scores will be examined for normality. If variable distributions deviate too much from normality, corrective steps will be taken either by transforming variables or by using non-parametric tests. We will control for child functioning, parental psychopathology, duration, severity, and intensity of interparental violence, and new IPV incidents. The variables are treated as covariables in the analyses mentioned below.

To examine our primary hypothesis, linear mixed models will be used in case of continuous data. GEE will be used for the categorical data. We will use the end of treatment (T12/T14) and intermediate/follow-up time-point (T13) to compare FITT with ITT (objective 1).

To examine our secondary hypotheses, linear mixed models will be used. We will use the end of treatment time-point (T12/T14) to compare FITT with TAU. Control measures are child functioning; parental psychopathology; duration, severity, and intensity of interparental violence; and new IPV incidents. The variables are treated as covariables in the up-mentioned analyses. We will use the Benjamini-Hochberg method to correct for multiple comparisons.

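### Table 4 labels FIT categorical but assigns a t-test meant for continuous measures, which also cannot carry the covariates the section promises

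*Protocol article*

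**What the plan says.** Section {20a} of the protocol article sets rules by type of outcome. For single-occasion outcomes: "Continuous measures with only one time point will be analysed with independent samples" t-tests. For categorical outcomes: "Changes in categorical outcomes over the course of treatment across the conditions are tested with generalized estimating equations (GEE". Later in the section, GEE is named again, in general terms, for categorical data under the primary hypothesis.

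The FIT row of Table 4 reads "FIT Categorical 1 Independent samples T-test".

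In Outcomes {12}, FIT stands under the Primary outcomes heading, in the part on emotional security and physical safety. Its scoring is described so: "Rating scales range from 1 to 5 and a higher score indicates a greater presence of that particular construct". In Table 3 the row "FIT 4 tasks cp Observation" is marked at T12/14 only, so FIT has no T0 score.

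On covariates, {20a} opens with an unrestricted statement that the analyses control for duration and severity of family violence, child functioning, parental psychopathology and "new incidents of family violence as a priori potential confounders". A later paragraph repeats the list and adds: "The variables are treated as covariables in the analyses mentioned below". What follows that sentence is mixed models and GEE. Section {16a} says that families are randomised within each site.

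**The concern.** Two statements about FIT do not fit together. Under the section's own rule the t-test belongs to continuous measures, while the table calls FIT categorical. An analyst who follows the label and one who follows the test could analyse the same outcome differently.

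The t-test also has no term for a covariate. If the opening covariate sentence covers all analyses, the FIT analysis breaks it. If FIT is exempt, the protocol does not say so or why. Site is left out too, although allocation is done within site.

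At stake is the only observational measure in Table 3, in an open-label trial whose other measures in this domain are questionnaires. The consequences are an avoidable choice of method at analysis and some loss of precision.

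**Working it through.** **1. Label against test.** FIT is scored on ordered 1–5 scales with one occasion. The t-test rule (continuous, one occasion) fits that description; the label does not. The other categorical row in Table 4, CAPS-CA, is given GEE. FIT is the only row where label and test disagree, so the label is the likelier error.

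**2. The plan's own sample size, for reference.** Inputs from Sample size {14}: f = 0.18, two groups, m = 2 measurements, ρ = 0.5, ε = 1, two-sided 5%, power 80%.

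- λ = f²·N·m/(1−ρ), with 1 and N−2 degrees of freedom.
- N = 62: power 0.796. N = 64: λ = 0.0324 × 64 × 2 / 0.5 = 8.294, power 0.809.
- The smallest even N is 64, as stated, or 32 per arm. For three arms, 3 × 32 = 96 and 96/(1−0.20) = 120, the stated target.

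No stated sample-size figure depends on how FIT is analysed.

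**3. Power for FIT at 32 per arm.** The document gives no FIT effect size, SD or covariate correlation, so all three are assumptions. For the t-test the noncentrality is d·√(n/2) = d × 4 on 62 df. Adjustment for covariates with combined correlation r replaces d by d/√(1−r²). For d = 0.5: 0.500, 0.524, 0.546 and 0.577 at r = 0, 0.3, 0.4 and 0.5.

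| Assumed d | t-test | r = 0.3 | r = 0.4 | r = 0.5 |
|---|---|---|---|---|
| 0.36 | 29% | 32% | 34% | 37% |
| 0.50 | 50% | 54% | 57% | 62% |
| 0.72 | 81% | 84% | 87% | 91% |

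**4. What the covariates cost.** Losing 5 residual degrees of freedom alone is trivial: at d = 0.5 and r = 0, power goes from 0.504 to 0.503. Chance association of q covariates with arm costs more. It inflates the variance on average by (N−3)/(N−q−3), taking the covariates as roughly normal. With q = 5 (violence duration, violence severity, child functioning, parental psychopathology, one Security Scale report) this is 61/56 = 1.089. At d = 0.5:

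- r = 0.3: 0.5/√(0.91 × 1.089) = 0.502, power 51%
- r = 0.4: 0.5/√(0.84 × 1.089) = 0.523, power 54%
- r = 0.5: 0.5/√(0.75 × 1.089) = 0.553, power 59%
- r = 0: power 47%, a small loss

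Break-even is r² = q/(N−3) = 5/61 = 0.082, or r ≈ 0.29. Site adds three columns for four centres. These cost little beyond degrees of freedom if the arms are close to balanced within site; otherwise break-even moves to 8/61 = 0.131, or r ≈ 0.36.

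**The case against.** The strongest reply is that the planned test is clear and only one word in a table is wrong. Much of this stands, and it rules out several stronger readings.

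- *A reader might infer that the categorical label obliges the trial to use GEE.* The GEE rule concerns change over treatment, and FIT has one occasion. Only the later general sentence on categorical data points to GEE.
- *A reader might infer that the later covariate sentence is broken.* The analyses that follow it are mixed models and GEE, not the t-test. The inconsistency rests on the opening, unrestricted sentence, whose scope for FIT is at best unclear.
- *A reader might infer that FIT gets the least precise analysis in the plan.* At the protocol's own ρ = 0.5, the variance of a pre–post change is 2(1−0.5)σ² = σ², the same as a post-only comparison. The t-test at d = 0.72 has noncentrality 0.72 × 4 = 2.88, and 2.88² = 8.294, exactly the λ of the planned design.
- *A reader might infer bias, or that a FIT baseline is being thrown away.* Randomisation makes the unadjusted comparison valid, and no FIT baseline is scheduled. The unused information lies in other T0 measures only.

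Two further points are fair. Site appears in no analysis in {20a}, so its absence is not special to FIT. Covariate detail may also sit in an analysis plan that is not shown. Neither removes the mismatch between label and test, or between a general promise to adjust and a method that cannot.

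**Conclusion.** The point holds as an internal inconsistency with a modest loss of precision; it is a desirable correction, not a threat to validity. The contradiction in Table 4 and the conflict with the opening covariate sentence can be read from the text and need no assumption.

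The size of the loss cannot be derived from the document. Assuming d = 0.5 and a correlation of 0.3–0.5 between the T0 covariates and FIT, power at 32 per arm rises from about 50% to 54–62% before the cost of the covariates. With five covariates the net figure is about 51–59%. If the covariates do not predict FIT, there is no gain and a slight loss. The case for the change is therefore mainly consistency with the plan's own rule, with precision as a possible extra that depends on a short, well-chosen covariate list.

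**What to change.** In Table 4, relabel FIT as continuous (or ordinal). Replace the t-test by a linear regression of FIT on arm, fitted separately for FITT versus intensive trauma treatment without the family component and for FITT versus TAU, with:

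- site;
- the plan's listed covariates as measured at T0: violence duration and severity, child functioning, parental psychopathology;
- if wanted, one T0 Security Scale report, stating in advance whether the child's or the parent's. The plan does not list this as a covariate, so it is an addition.

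Leave out new incidents after randomisation. They may be affected by treatment, and adjusting for them could remove part of the effect. State this as a deliberate departure from the listed set. Choose one scale per covariate and keep the set small for about 32 per arm.

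If the team prefers the t-test, the minimum is to correct the label and state that FIT is exempt from covariate adjustment, and why.

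The cost is wording only, since the T0 measures are already scheduled in Table 3. The change should be fixed before anyone sees outcome data by arm.

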### Eligibility criteria {10}

Children are eligible to participate in the study if they meet the following inclusion criteria: (a) the child has been exposed to family violence; (b) the acute safety in the family has been established; (c) the child is between 12 and 20 years old; (d) the child lives at home with its caregiver(s); (e) caregivers, living with the child can participate in the systemic components; (f) the child has posttraumatic stress symptoms, at least intrusions and avoidance; and (g) caregivers and children master the Dutch language. The exclusion criteria for participating in the study are (a) children and caregivers who have acute psychotic symptoms or severe alcohol and drug addictions and (b) children with a suicide attempt in the past 3 months. The in- and exclusion criteria are established with an intake interview with a trained therapist and standardized questionnaires.

All therapists participating in the study are trained in the overall treatment program and have additional training in the part of the treatment program they will perform. Exposure therapy will be performed by therapists who have basic training in cognitive behavioural therapy. EMDR therapy will be performed by the therapists who completed the advanced EMDR training (VEN, Dutch EMDR Association). The bodily oriented therapy is offered by psychomotor therapists or therapists with experience in trauma and bodily oriented therapy under the supervision of an experienced psychomotor therapist. Parent therapy is performed by a family therapist or family worker. Together with a child therapist, the family therapist/worker will also offer the family sessions.

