#### Primary outcomes

##### Child PTSD symptoms

The Clinician-Administered-Ptsd-Scale-Children-And-Adolescents (CAPS-CA) [55] is a standardized clinical interview, to assess PTSD conform the DSM-5 standards. A Dutch translation of the CAPS-CA [56] is administered to children aged 8–18. The core traumatic event is chosen based on the life events checklist. If the core traumatic event is a sequence of events, which is often the case in family violence, a brief term is chosen to capture the core of these events. The CAPS-CA assesses the frequency and intensity in which each PTS disorder symptoms occur. A 5-point severity rating scale is used for all symptoms, ranging from 0 (= absent) to 4 (= extreme/incapacitating). An example item is *In the past month, have you had upsetting thoughts, pictures or sounds of what happened come into your mind when you didn’t want them to?*. A total symptom severity score is calculated by summing the severity scores for items 1–20. A total symptom score can also be calculated per cluster; re-experiencing (items 1–5), avoidance (items 6 and 7), negative alterations in cognitions and mood (items 8–17), and hyperarousal (items 15–20). A symptom cluster score may also be calculated for dissociation by summing items 29 and 30. To determine the PTSD diagnostic status, individual symptoms should be dichotomized as “present” or “absent”. A symptom is considered present only if the corresponding item severity score is rated 2 (= moderate/threshold or higher). Items 9 and 11–20 have the additional requirement of a trauma-relatedness rating of definite or probable. The DSM-5 diagnostic rule requires the presence of at least one criterion B symptom, one criterion C symptom, two criterion D symptoms, and two criterion E symptoms. Also, criteria F (disturbance at least 1 month) and G (disturbance that causes either clinically significant distress or functional impairment) must be met. Reliability of the CAPS-CA in a Dutch sample for the total scale ranged from coefficient *a* of 0.77 to .86, and the interrater reliability of the total scale is 0.99. Caps-CA also demonstrated divergent, convergent, and discriminant validity [57].

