#### Sample size {14}

Power analysis was conducted to determine whether an informative trial could be conducted given limitations imposed upon the maximum sample due to the duration of the study and size of the population of children indicated for trauma treatment, using G*power 3 [95]. Sample size calculation was made based on the assumptions of the primary objective and the first secondary objective. A priori, we decided that adding systemic intervention elements to individual trauma therapy would be justified if it would mean that on average at least one out of five children would have clinically significant benefit when given the full FITT compared to treatment without systemic elements (number needed to treat = 5; equivalent to *f* = 0.18).

For primary objective 1 (Does intensive trauma therapy with a family-based component (FITT) lead to a stronger reduction of trauma symptoms and stronger increase of structural emotional safety than intensive trauma therapy without this family-based component (ITT)?), the sample size was calculated based on between 2 groups by within effect with at least two measurements (pre, end/follow-up), setting *f* = 0.18 with a power of 80% and a significance level of 5% (two-sided). Default settings were used for the correlation among repeated measures (= 0.5) and non-sphericity correction (*ε* = 1). According to the power analysis, a total sample size of 64 children is required.

Secondary objective 1 (Does intensive trauma therapy with a family-based component (FITT) lead to faster reduction of trauma symptoms and increase of structural emotional safety than low-frequency trauma treatment with parent therapy and family sessions?) is based on two measurements (pre and intermediate/follow-up). In accordance with the first sample size calculation, we tested with setting *f* = 0.18 with a power of 80%, a significance level of 5% (two-sided) was used. Again, default settings were used for correlation among repeated measures (= 0.5) and non-sphericity correction (*ε* = 1). Based on this calculation, a total sample size of 64 children is required.

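### Table 4 types CAPS-CA only as categorical (GEE) and no section gives its 20-item severity total a model, so the stated 80% power does not apply to that measure

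*Protocol article*

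**What the plan says.** **Measure.** CAPS-CA is listed first under the primary outcome Child PTSD symptoms and is the only interview in that domain. The Outcomes section describes two results from it:

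- a score: "A total symptom severity score is calculated by summing the severity scores for items 1–20". Each item is rated 0 to 4, so the range is 0 to 20 × 4 = 80;
- a category: "To determine the PTSD diagnostic status, individual symptoms should be dichotomized as “present” or “absent", followed by the DSM-5 rule.

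**Analysis.** In Statistical methods {20a} the general rule is "Changes in categorical outcomes over the course of treatment across the conditions are tested with generalized estimating equations (GEE"), and for the primary hypothesis "GEE will be used for the categorical data", with linear mixed models for continuous data. Table 4 has a single CAPS-CA row: "CAPS-CA Categorical 3 GEE ITT/PP". CRIES and TSCC, the other two Child PTSD measures, are typed continuous and go to mixed models.

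**Sample size.** Section {14} uses "between 2 groups by within effect with at least two measurements (pre, end/follow-up"), f = 0.18, correlation 0.5, 80% power and two-sided 5%, giving 64 children for FITT against ITT (the intensive treatment without the family component). There is no calculation for a binary outcome.

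**Schedule.** Table 3 marks CAPS-CA at T0 and T13 only. Section {20a} compares FITT with ITT at T12/T14 and T13, and FITT with TAU at T12/T14.

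**The concern.** The primary question in Objectives {7} asks whether FITT reduces trauma symptoms more than ITT does. That is a matter of degree, and the severity total measures it directly. A yes/no diagnosis keeps only whether a child crosses a line.

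Entry does not require a diagnosis: the criterion is that "the child has posttraumatic stress symptoms, at least intrusions and avoidance", whereas the DSM-5 rule also needs D and E symptoms and criteria F and G. A child who enters below the diagnostic line cannot show improvement on diagnosis. The article does not say how many such children to expect.

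The trial is open-label and the other two PTSD measures are questionnaires, so the interview has particular value. As Table 4 stands, it gets the less sensitive analysis, and the power statement does not cover it. The CAPS-CA row also implies an assessment that Table 3 does not schedule.

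**Working it through.** **Inputs from Sample size {14} and Trial design {8}:** f = 0.18; 2 groups; m = 2 measurements; correlation ρ = 0.5; two-sided α = 0.05; N = 64 for two arms, so 32 per arm; 96 completers and 120 randomised in three arms. **Not in the article:** PTSD rates by arm. These are assumed and shown as a range.

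**1. The plan's own figure.** For the within-between interaction, λ = f²·N·m/(1 − ρ) = 0.0324 × 64 × 2/0.5 = 8.29, with 1 and 62 degrees of freedom. Power is 80.9% (N = 62 gives 79.6%). The stated 64 reproduces, as does 3 × 32 = 96 and 96/0.8 = 120. The calculation is for a difference in mean change.

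**2. The effect in SD units.** For two equal groups, d = 2√(λ/N) = 2√(0.0324 × 4) = 0.72 on the change score. The SD of change is σ√(2(1 − ρ)) = σ at ρ = 0.5, so this is also 0.72 SD of the score.

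**3. Severity total, 32 per arm.**
- Change score: about 81%.
- Adjusted for baseline: the residual SD is √(1 − 0.25) = 0.866, so the effective difference is 0.72/0.866 = 0.83 SD. Power is about 90%, confirmed by simulation.

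**4. Diagnosis, same effect, 32 per arm.** Treat diagnosis as a cut on a normal severity score. If the control rate after treatment is p_C, then p_F = Φ(Φ⁻¹(p_C) − 0.72). The power of the two-proportion test is Φ{[(p_C − p_F)√n − 1.96√(2p̄(1 − p̄))] / √(p_C(1 − p_C) + p_F(1 − p_F))}, where p̄ is the mean of the two rates.

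| Assumed PTSD rate, ITT | Implied rate, FITT | Power, 32 per arm | n per arm for 80% |
|---|---|---|---|
| 30% | 11% | 48% | 67 |
| 40% | 17% | 55% | 57 |
| 50% | 24% | 60% | 52 |
| 64% (best case) | 36% | 62% | 49 |
| 80% | 55% | 58% | 54 |

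The score needs 31 to 32 per arm. Simulation with cuts at −0.5, 0 and +0.5 SD around the control mean gives about 65%, 61% and 50%.

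**5. Like for like.** Baseline adjustment must go to both sides or to neither.

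| | Severity total | Dichotomised | Gap |
|---|---|---|---|
| Unadjusted | 81% | 50–65% | 16–31 points |
| Adjusted for baseline severity | 90% | 55–68% | 22–35 points |

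**6. Rough check with GEE itself.** This used 250 runs per setting and assumed a 1 SD improvement in the control arm, with baseline PTSD rates of 62% to 91%. Power was 25–37% for a group-by-time interaction and 35–70% with a common baseline. The result depends on the assumed rates and on how the baseline is handled.

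**7. Time points.** Table 3 gives CAPS-CA two occasions (T0, T13) and Table 4 gives three. If Table 3 holds, CAPS-CA has no value for either T12/T14 comparison in {20a}.

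**The case against.** **The label may be a slip.** The general GEE sentence does not name CAPS-CA. Table 4 is loosely typed elsewhere: FIT is called categorical yet gets a t-test, which the text reserves for continuous measures, and TSI appears where Table 3 has IES-r. Under the rule that continuous data go to mixed models, the severity total would belong there. This stands as an explanation. A reader might infer a deliberate decision to discard the score, and the article does not show that. But Table 4 is the only place that assigns CAPS-CA an analysis, and it assigns only this one.

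**A binary outcome suits the rationale.** Section {14} justifies the trial by a number needed to treat of 5, which is a responder idea. That is a good reason to keep diagnosis. However, nothing equates diagnosis with the clinically significant benefit meant there. Read directly as a 20-point difference in PTSD rates, 32 per arm gives only 36–52% power over control rates of 30–80%.

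**The primary domain is not left without power.** CRIES and TSCC remain continuous. This stands and limits the point to one of three PTSD measures.

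**Missing data.** A reader might infer that the plan commits to a GEE valid only under data missing completely at random. The text does not support that. It says "For the planned GEE, we will explore the possibilities to deal with missing data" and makes the choice depend on the amount, randomness and type of missing data. The detail can properly sit in an analysis plan.

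**Conclusion.** The point holds as a should-fix. The article gives the severity total of its only PTSD interview no analysis, although that total matches the primary question and the type of outcome used for the sample size. Dichotomising costs about 16–31 points of power unadjusted, or 22–35 points with baseline adjustment on both sides. The stated 80% therefore does not describe the categorical CAPS-CA analysis.

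The size rests on 32 per arm, ρ = 0.5, the 0.72 SD effect implied by f = 0.18, a cut on a normal score in place of the DSM-5 symptom-count rule, and assumed PTSD rates. At half that effect (0.36 SD) power is low either way, about 29% for the score against 18–22% for the category, both unadjusted.

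Three stronger readings are not supported:
- that the loss is 25–40 points, which comes from setting a baseline-adjusted score against an unadjusted proportion;
- that the primary question as a whole loses its continuous analysis;
- that Table 4 is the table in error on time points. The two tables conflict, and the article does not show which is right.

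**What to change.** 1. Split the CAPS-CA row of Table 4. Make total severity (items 1–20) the main CAPS-CA analysis: continuous, in the planned linear mixed model with maximum likelihood and baseline severity taken into account. Keep PTSD diagnostic status by GEE as supportive.
2. State in Sample size {14} that the 80% refers to the continuous outcome and does not extend to diagnostic status.
3. Reconcile Table 3 with Table 4. If Table 3 is right, Table 4 should show 2 time points and CAPS-CA should be excluded from the T12/T14 comparisons in {20a}. If three interviews were intended, Table 3 needs the missing occasion.

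The cost is an edit to the table and text, made before analysis. The items behind the severity total are already rated at each interview, so step 1 needs no new data. Only the second outcome of step 3 would add an interview to the schedule in Table 3.

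### Testing change in CAPS-CA diagnosis by GEE makes T0 a response and so adds noise; a T13 comparison adjusted for T0 severity is the better test

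*Protocol article*

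**What the plan says.** Statistical methods {20a} gives one sentence on categorical outcomes: "Changes in categorical outcomes over the course of treatment across the conditions are tested with generalized estimating equations (GEE". In Table 4 the CAPS-CA row reads "CAPS-CA Categorical 3 GEE", and no other row names GEE.

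Table 3 (Outcomes {12}) lists the same instrument as "CAPS-CA c Interview" and marks it at T0 and T13 only, so Table 4 counts one time point more than Table 3.

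The outcome section on child PTSD symptoms gives CAPS-CA a total severity score and also a yes/no diagnosis: "To determine the PTSD diagnostic status, individual symptoms should be dichotomized". The rule needs "at least one criterion B symptom, one criterion C symptom, two criterion D symptoms, and two criterion E symptoms", plus criteria F and G.

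Entry criterion "f) the child has posttraumatic stress symptoms, at least intrusions and avoidance" overlaps with two of those clusters. It does not ask for a diagnosis.

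Sample size {14} sets the worthwhile benefit at "number needed to treat = 5" and converts it to f = 0.18 for a continuous repeated-measures calculation.

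**The concern.** A between-arm difference in change of a binary status is, in a logit GEE, the arm-by-time term:

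interaction = logOR(T13) − logOR(T0).

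The arms are randomised, so the true logOR(T0) is zero. Putting T0 on the response side means estimating a known zero and subtracting the estimate. That adds variance unless T0 and T13 status are correlated strongly enough to offset it. The added variance is driven by the T0 non-cases, and selection on intrusions and avoidance tends to make those fewer. If every child in one arm is a case at T0, the term cannot be estimated.

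CAPS-CA is the only interview among the primary PTSD measures. At stake is whether its categorical analysis makes good use of the T0 data. There is also a question of reading: an interaction odds ratio does not translate into a benefit of the one-child-in-five kind, whereas a risk difference does.

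**Working it through.** **1. The plan's own figure.** Sample size {14} uses f = 0.18, two groups, two measurements, correlation 0.5, ε = 1, two-sided 5% and 80% power. With λ = f²·N·m/(1−ρ) = 0.18² × 64 × 2/0.5 = 8.29 on 1 and 62 degrees of freedom, power is 0.809. 64 is the smallest even N reaching 0.80, so the figure is reproduced: 32 per arm. Three arms give 96, and 96/0.8 = 120, or 40 randomised per arm. This calculation is for a continuous outcome and does not cover diagnosis.

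**2. Plain comparison at T13.** Assumed: 32 per arm, diagnosis 50% versus 30%.
- logOR = ln(0.5/0.5) − ln(0.3/0.7) = 0.847.
- Variance = 1/(32×0.5×0.5) + 1/(32×0.3×0.7) = 0.125 + 0.149 = 0.274; SE 0.52.
- Power = Φ(0.847/0.523 − 1.96) = Φ(−0.34) ≈ 37%. Simulation of the Wald test gives about 39%.

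**3. Interaction test.** The T0 part adds V0 = 2/(32·p0·(1−p0)), less twice the covariance. With no T0-T13 correlation:
- p0 = 0.80: V0 = 0.391, SE = √(0.274+0.391) = 0.82, power Φ(0.847/0.815 − 1.96) ≈ 18%.
- p0 = 0.90: V0 = 0.694, SE = 0.98, power ≈ 14%.
- p0 = 0.95: V0 = 1.316, SE = 1.26, power ≈ 10%. This approximation is too kind, because it ignores trials with no estimate.

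Correlation helps little at high prevalence. The largest possible phi between two binary variables with prevalences p0 > p1 is √[p1(1−p0)/(p0(1−p1))]. For p0 = 0.90 and p1 = 0.50 that is √(0.1/0.9) = 0.33.

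Simulation used 20,000 trials per scenario, complete data with 32 per arm, robust SE, and phi from 0 to 0.6 capped at its maximum. Trials with no estimate count as non-significant. The last two columns are 1 − (1 − p0ⁿ)².

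| T0 prevalence | Median SE of interaction | Power | An arm all cases, n = 40 | n = 32 |
|---|---|---|---|---|
| 80% | 0.66-0.84 | 18-27% | 0.03% | 0.2% |
| 90% | 0.91-1.03 | 11-14% | 2.9% | 6.7% |
| 95% | 1.21-1.28 | 3-4% | 24% | 35% |

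The median SE for T13 alone is 0.53. An SE of 1.0 means a 95% interval for the odds ratio spanning a factor of exp(2×1.96) ≈ 50.

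**4. Lower prevalence and other effects.** The scenarios were widened to T13 pairs of 30/50%, 40/60% and 20/50%, with 32 or 40 per arm. The relative loss of power against the plain T13 test is then:
- 95%: 80-92%
- 90%: 51-74%
- 80%: 23-56%
- 70%: from none to 51%
- 50-60%: from a gain of about 23% (phi 0.6) to a loss of 47% (phi 0)

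**5. T13 comparison adjusted for T0 severity.** With 32 per arm, 50% versus 30%, latent correlation 0.3 to 0.8 and T0 prevalence 50% to 95%, this beat the interaction test throughout. At latent correlation 0.5 the powers were 41% versus 30% (prevalence 50%), 42% versus 21% (80%) and 42% versus 4% (95%).

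**The case against.** **The contrast is not written out.** {20a} names neither link nor model terms. It later lists T12/T14 and T13 as the points for comparing FITT with ITT, which could mean a comparison at those visits. Such detail is often left to an analysis plan. This stands in part. But the sentence on change is a stated choice, and the list of visits does not withdraw it. With CAPS-CA at T0 and T13 only, a repeated-measures GEE has to take T0 as a response.

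**A reader might infer that nearly all children are cases at entry, so that most of the power is certain to be lost.** The documents do not support that. Entry requires intrusions and avoidance, not the D, E, F and G criteria, and no T0 prevalence is given. The Background cites 21% with clinical symptoms in a referred sample. That sample is not described as selected on the entry criterion, so it settles nothing either way.

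**At 50-60% prevalence with high correlation the interaction test can win.** True, but only against the unadjusted T13 comparison. It did not beat the adjusted one.

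**A reader might take the number needed to treat of 5 as a 20-point difference in diagnosis.** The protocol ties it to clinically significant benefit in general. The 50% versus 30% used here is an assumption.

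**The remedy leaves power near 40%, and CRIES and TSCC are continuous primary PTSD measures analysed by mixed models.** Both are true. The PTSD question does not rest on this test alone, and low power for a binary outcome at this sample size is a separate matter. Neither is a reason to give up more power.

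**Conclusion.** The point holds as a conditional one. On the natural reading of {20a} and Table 4, the CAPS-CA test estimates a T0 difference already known to be zero in expectation and so mainly adds noise. With 32 per arm and 50% versus 30% at T13, power falls from about 37-40% to 18-27%, 11-14% or 3-4% if 80%, 90% or 95% of children are cases at T0. Below that range the comparison with a plain T13 test can go either way. Failure to estimate is negligible at 80% or less. With the 40 per arm randomised, it is about 3% at 90% and 24% at 95%.

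These figures rest on assumed prevalence, correlation and T13 rates, none of which the protocol gives. The choice of remedy depends on them much less, since adjusting for T0 severity did at least as well in every scenario checked. The change should be made, but nothing here invalidates the trial.

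**What to change.** For CAPS-CA diagnosis, replace the GEE test of change by logistic regression of T13 status on arm, with the T0 CAPS-CA severity score as covariate. Report the arm effect also as a risk difference at T13, for example by averaging predicted risks over the observed T0 scores.

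If GEE is kept because there are several post-baseline visits, model only those visits as responses and enter T0 severity as a covariate.

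Reconcile Table 4 (three CAPS-CA time points) with Table 3 (T0 and T13), and state the tested contrast in words.

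Cost: a few sentences in {20a} and one row of Table 4. The T0 severity score is already collected; no extra data or participants are needed.
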